***Informed Consent and Pre-delivery Procedures***

Informed consent will be obtained by trained study personnel after women have been admitted to the hospital and upon arrival at the labor ward. If study personnel feel that the woman is too far advanced in her labor to give appropriate informed consent, she will not be eligible for enrollment. Women who decline to participate in the study will be given full medical care according to standard practice in the facility. Women who wish to participate will be asked to read and sign the informed consent form. If the woman is unable to read, the form will be read and explained to her, and her consent will be indicated by a mark, such as the woman’s thumbprint. If at any point during her participation in the study the woman indicates that she no longer wishes to continue, she will be withdrawn from further data collection.

Background characteristics and baseline data will be obtained and documented on Form 1. Pre-delivery hemoglobin will be measured and recorded for all women, using a Hemocue® Hemoglobin machine + cuvette (HemoCue, Ängelholm, Sweden).

***Randomization and Enrollment***

All participants will be randomized to prophylactic management with oxytocin in the third stage of labor either via IV infusion or IM injection, with the assignment contained in sequentially numbered sealed opaque envelopes. During the second stage, prior to each woman’s delivery, study personnel will open the next sequential randomization packet containing her study group assignment. Since the study will be blinded and placebo-controlled, study personnel will open the next sequential drug packet, which will contain a vial each of 10 IU oxytocin and 10 IU matching placebo. Each vial will have an affixed label indicating the assigned route of administration of the contents.

10 IU oxytocin ampoules and similar placebo ampoules (containing 10 IU of saline) will be prepared by a local laboratory / pharmacist. The ampoules prepared for the study (e.g. study packets) will have to be stored in a refrigerator to maintain the cold chain necessary for oxytocin until the time of administration to the mothers. The randomization code will be generated in advance by Gynuity Health Projects staff in New York. The random assignment will be made in blocks of 10 and will be generated with a computer program. Only the Gynuity study coordinator will have access to this randomization scheme. Once an administration assignment has been allocated, the woman will be considered an enrolled participant.

Study staff will observe women and will record any intervention, including other AMTSL components performed during delivery. In addition, staff will note whether a woman has had her labor induced or augmented prior to delivery and, if possible, the drug used and time administered. In the case of labor augmentation with oxytocin, it should also be noted that the agent was discontinued upon delivery of the fetal head.

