**Description of Research**

This double-blind, controlled and randomized study will be carried out in a hospital where policy dictates that all women should receive 10 IU of prophylactic oxytocin in the third stage of labor. Furthermore, the majority of women who give birth in the study hospital already have an IV line in place. The study objective will be to evaluate the impact of route of administration of 10 IU oxytocin on postpartum bleeding. Eligible women who provide informed consent and give birth vaginally will be randomized to receive either:

- 10 IU oxytocin via IV infusion
- 10 IU oxytocin via IM injection

Oxytocin 10 IU will be administered either by IV infusion or IM according to randomization assignment as soon as possible after delivery of the baby. The IV infusion will be done by placing 10 IU of oxytocin in a bag of saline solution of 500 cc and then administered over 40 minutes (eg, 12cc/min or 240drops/min). All study participants will receive oxytocin by IV infusion or by IM injection, based on randomized allocation, and the corresponding placebo by the non-assigned route.

To avoid any potential bias that knowledge of the route of administration of oxytocin may have in the quantification of blood loss, study staff members and participants will not know the assignment of the route of administration of the active drug. Since all delivering women in the study hospital routinely have an IV line in place, all study participants will receive oxytocin by either IV infusion or IM injection, based on randomization assignment, in addition to placebo by the non-assigned route. Blood loss will be measured in a calibrated container for 1 hour. If a woman experiences excessive bleeding or PPH, she will receive treatment according to standard of care at the study site.

Independent of the diagnosis of PPH, consenting women who have a vaginal delivery will have their postpartum blood loss measured using a standardized receptacle, in addition to other indicators and outcomes recorded during the immediate postpartum period to assess the relationship between shock index and PPH outcomes. Blood loss will be measured for 1 hour, and if PPH diagnosed, measurement will continue until cessation of active bleeding. Pulse and blood pressure will be measured at pre-defined intervals (15, 30, 45, and 60 minutes) in order to document hemodynamic changes that occur during the immediate postpartum period.

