**Data Management and Monitoring**

Copies of all study forms for the first five women enrolled will be sent to the study coordinator at Gynuity Health Projects for review prior to continuation of enrollment. Thereafter, copies of the forms will be sent periodically to the Gynuity Health Projects in New York. All original forms will be retained at the study site.

Data will be entered into an SPSS database for subsequent review of logical inconsistencies, cleaning, and analysis.

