***Analysis and Dissemination of Results***

Bivariate analyses will be conducted, stratified by study arm. Unadjusted and adjusted logistic regression will be conducted respectively for categorical and continuous dependent variables.

To compare the two study arms (oxytocin IM vs. oxytocin infusion), the main analyses will include:

- Mean postpartum blood loss (primary outcome)
- % of women with blood loss ≥500 ml (primary outcome)
- Median postpartum blood loss and interquartile range
- % of women with blood loss ≥1000 ml,
- Mean change in Hb measured pre- to post-delivery
- % of women with postpartum Hb drops of 2 g/dl or greater
- % of women with prolonged third stage of labor
- % of women who received additional oxytocics or other interventions to manage bleeding
- % of women who experienced side effects

We will register use of any other AMTSL components, such as controlled cord traction, uterine massage, etc. that are used.

In order to assess the relationship between shock index and severity of bleeding, we will correlate shock index values, heart rate, and blood pressure measures to blood loss levels that will be recorded at 15, 30, 45, and 60 minutes following delivery. Absolute values and measured changes in these values during the first hour following delivery will be analyzed. We will also explore associations between these clinical signs/symptoms with other PPH outcomes, including provision of additional interventions to control bleeding, blood transfusion, and other severe outcomes.

Data will be owned by Gynuity Health Projects. The principal investigators and study coordinators will work together to analyze the results of the study and prepare at least one manuscript for submission to one or more relevant peer-reviewed journals. In addition, members of the study team will present the results of the study at conferences and meetings where appropriate. All principal investigators will be named along with key Gynuity staff as authors of any publications or presentations describing results from the study.

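### The protocol gives two unreconciled allocation procedures; one, followed literally, tells bedside staff the active route and contradicts the blinding statement

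*Protocol*

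**What the plan says.** The protocol, Description of Research, makes the claim: "This double-blind, controlled and randomized study will be carried out in a hospital". It then says who is blinded, "study staff members and participants will not know the assignment of the route of administration of the active drug", and why: "To avoid any potential bias that knowledge of the route of administration of oxytocin may have in the quantification of blood loss". The means is a double-dummy: each woman receives active drug by one route and placebo by the other.

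The Randomization and Enrollment section describes how a woman gets her allocation, in two ways.

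- **Envelope procedure.** Assignments sit in numbered, sealed, opaque envelopes. In the second stage of labor, "study personnel will open the next sequential randomization packet containing her study group assignment".
- **Drug-packet procedure.** The next two sentences say that, because the trial is blinded, staff open the next drug packet in sequence. It holds one oxytocin vial and one matching placebo vial, each labelled with the route by which it is to be given.

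On code access the same section says: "Only the Gynuity study coordinator will have access to this randomization scheme". Data Management and Monitoring says: "Copies of all study forms for the first five women enrolled will be sent to the study coordinator at Gynuity Health Projects for review"; later forms go to the sponsor organisation, with no role named. Analysis and Dissemination of Results says: "The principal investigators and study coordinators will work together to analyze the results of the study". On the list itself: "The random assignment will be made in blocks of 10".

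**The concern.** The study groups are IV infusion and IM injection of the active drug. A document that holds a woman's study group is therefore a document that states the active route. If study personnel open it before delivery, they know what the blinding statement says they will not know.

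Both primary outcomes, mean blood loss and the proportion losing at least 500 ml, come from a container read at the bedside. The Intervention section also leaves providers discretion: they may diagnose PPH whenever they judge it present, and a diagnosis starts standard treatment and continued measurement. Knowledge of the route could therefore act on the reading, on the decision to treat and on how long blood is collected. The protocol itself names bias in measuring blood loss as its reason for blinding.

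A separate question is whether the person who holds the code is kept apart from data review and analysis.

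**Working it through.** The plan states no figure on this point, so there is none to reproduce. The check is a comparison of texts, with one conditional calculation.

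**Step 1. Can both statements be followed?**

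| Question | Description of Research | Envelope procedure | Drug-packet procedure |
|---|---|---|---|
| What do staff open? | not stated | envelope or randomization packet | numbered drug packet |
| What is inside? | not stated | the woman's group | one active and one placebo vial, route-labelled |
| Do staff learn the active route? | no | yes, read literally | no, if labels do not identify the contents |

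The envelope procedure conflicts with the blinding statement. The drug-packet procedure agrees with it, on one condition that the text does not settle: the label is said to give the route, but not said to hide whether the vial is active or placebo. Nor does the text say whether the envelope, the randomization packet and the drug packet are one item or several.

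**Step 2. What follows at a site?** Staff who carry out every sentence open the group assignment and then the drug packet, and are unblinded for every woman. Staff who treat the drug packet as the only item opened stay blind, given masked labels. Both can claim to follow the protocol.

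**Step 3. Predictability of the next allocation, only if past assignments are visible.** Blocks are fixed at 10, so there are m = 5 assignments per arm in each block.

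- Expected correct guesses per block under the best guessing rule: m + (2^(2m)/C(2m,m) − 1)/2 = 5 + (1024/252 − 1)/2 = 6.53 of 10, or 65%.
- Expected assignments known with certainty: 2m/(m+1) = 10/6 = 1.67 of 10, or 17%. Enumerating all 252 balanced sequences gives the same 1.67.
- Scaled to the planned 486 women: 486 × 1.67/10 ≈ 81.

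These figures describe the envelope procedure. With masked packets past assignments are not visible, and the figures do not arise. They measure how well the next allocation can be guessed, not bias in blood loss.

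**Step 4. Role of the code holder.**

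- Holds the code: the sponsor's study coordinator, alone.
- Reviews forms: the same role, stated for the first five women, 5/486 ≈ 1% of the sample. The Randomization/Delivery form carries the randomization number (Study Documentation), so a code holder can look up the arm.
- Analyses: principal investigators and study coordinators, in the plural. That the code holder is among them is a fair inference, not a statement.

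No sentence separates code access from review or analysis.

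**The case against.** The strongest answer is that this is loose wording. The sentence straight after the disputed one gives both the procedure and its reason, and Description of Research states the double-dummy twice. On a natural reading the drug packet is how the assignment is carried, and no one at the bedside reads a group name. This stands as far as intent goes: a reader might infer from the envelope text that the trial is in effect open-label, and the document does not support that. It does not remove the conflict, because the envelope text is still an instruction to staff and nothing withdraws it.

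The calibrated container and the fixed 500 ml prompt for diagnosis also limit discretion. They narrow the route for bias without closing it, since providers may diagnose PPH earlier and someone must still read the container.

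Three further inferences should be resisted.

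- **That the coordinator's role breaks the double-blind claim.** The blinding statement covers study staff and participants and is tied to measuring blood loss. Someone must hold the code, and the sponsor's coordinator is not described as reading the container. The protocol assigns that role review of five women's forms, not of all data during accrual. Custody rules may also stand in a document that is not shown.
- **That the local pharmacist must know the scheme, so the access rule cannot hold.** The protocol says who prepares the ampoules, not who applies the route labels.
- **That blocks of 10 are themselves a defect.** With masked packets opened in sequence, varying the block size would add little.

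**Conclusion.** The point holds as a contradiction between two parts of the protocol. Randomization and Enrollment contains an operative instruction that, followed as written, tells study personnel the active route, against the blinding statement in Description of Research. It also contains a second procedure that keeps the blind, and it does not say which one governs.

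The consequence is conditional. If only the drug packet is opened and its labels hide the contents, blinding is kept. If the envelope procedure is followed, staff are unblinded for all women, and both primary outcomes are exposed to biased measurement and treatment. The documents give no basis for the size of that bias. The figures of 65% and 17% (about 81 of 486) hold only if past assignments are visible and should not be cited otherwise.

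The missing separation between code custody, form review and analysis is a secondary weakness, not a contradiction of the double-blind claim. It rests partly on the inference that the code holder is among the coordinators who analyse the results.

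**What to change.** **Main change, before any packet is opened.** In Randomization and Enrollment:

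1. Delete the text that places assignments in envelopes, and remove from the sentence "study personnel will open the next sequential randomization packet containing her study group assignment" the closing words that say the packet holds the group.
2. State that the sequentially numbered drug packet is the only allocation carrier and the only item opened.
3. State that each vial label shows the route but not whether the contents are active or placebo.

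This costs a few sentences of protocol wording, with no extra women, drug or staff.

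**Secondary change.** Give custody of the code to an existing sponsor staff member who neither reviews forms nor analyses data until database lock. The small downside is that the coordinator loses access to the code during the trial.

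The block size can stay as it is.

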***Intervention***

Oxytocin 10 IU will be administered either by IV infusion or IM according to randomization assignment as soon as possible after delivery of the baby.

Immediately following delivery of the baby (or last baby, in the case of multiples), blood loss will be measured in a calibrated container for 1 hour. Blood loss will be recorded when active bleeding stops or at 1 hour, whichever is later. In the case of excessive bleeding or PPH requiring treatment, blood loss will be documented also at time of diagnosis. At delivery, some blood can be expected to spatter on the drapes and on the gowns of the attendant, and all attempts will be made to minimize such losses. Additionally, the placental interstices contain maternal blood (about 9% of the placental weight). We expect that overestimations (amniotic fluid) and underestimations (blood loss) are likely to be distributed between the two study arms; therefore there will be no need for corrections to the blood measurement for these inaccuracies.

If a woman experiences excessive bleeding or PPH and requires treatment, she should receive treatment according to standard of care at the study site. If PPH is diagnosed, measurement will continue until the bleeding stops. Health providers can diagnose PPH at any time, but if blood loss reaches 500 ml according to the marking on the calibrated container, PPH should be diagnosed and standard hospital treatment initiated.

The study staff will keep the participants under observation and record all interventions performed during delivery, including the prophylactic oxytocin administration of the study. Also, note if the delivery was induced or stimulated before delivery and if possible, the medication provided, and the time and dose in which it was administered. The provider will be asked to monitor the woman for side effects for 1 hour after delivery. Women will also respond to questions about side effects prior to discharge from the hospital.

In order to document changes in shock index values during the first hour after delivery, the heart rate and blood pressure of all women enrolled at 15, 30, 45 and 60 minute intervals will be recorded. These measurements will be taken independently of the diagnosis of PPH and the exact time of each measurement will be recorded. Automatic devices will be provided to all study centers to measure blood pressure and heart rate in order to standardize such measurements.

Post-delivery hemoglobin using a Hemocue® Hemoglobin machine + cuvette will be taken at least 24 after delivery and before the woman leaves the facility. If the woman has received IV fluids, hemoglobin will be measured at least 12 hours after removal of the IV prior to discharge.

***Study Documentation***

*Admission*. This form will document basic demographic characteristics and medical and obstetrical history to assess women’s eligibility for study participation. It will also document that each woman has signed the informed consent form. This form will be completed for all consenting women.

*Randomization/Delivery*. This form will document randomization number and relevant information during and post delivery, including time of delivery and events or interventions during the third stage of labor, especially with regard to administration of uterotonic agents as well as other components of active management. This form will also record any diagnosis of PPH. The form will be completed for all consenting women.

*Follow-up.* This form will be used to record information on side effects, adverse events, or problems following delivery at follow-up prior to discharge from the hospital. Post-delivery hemoglobin will be measured and recorded at this time.

*Severe Adverse Events (SAEs) Form*. This form will be used to document any SAEs as defined below. It should be completed by the principal investigator and forwarded to Gynuity Health Projects staff within 24 hours of his/her awareness of the event.

A serious adverse event is defined as one causing:

- Prolonged hospitalization;
- Permanent or serious disability;
- Additional threat to life; or
- Death.

**Data Management and Monitoring**

Copies of all study forms for the first five women enrolled will be sent to the study coordinator at Gynuity Health Projects for review prior to continuation of enrollment. Thereafter, copies of the forms will be sent periodically to the Gynuity Health Projects in New York. All original forms will be retained at the study site.

Data will be entered into an SPSS database for subsequent review of logical inconsistencies, cleaning, and analysis.

***Data and Safety Monitoring***

Gynuity Health Projects will monitor the progress of each site participating in the study. Trained monitors will visit sites a minimum of two times during the study to observe practices and review documentation to verify that:

- The rights and well-being of human subjects are protected;
- Data are collected according to the protocol, are accurate, complete and of the highest quality and integrity;
- Trial is in compliance with the approved protocol and Good Clinical Practices.

Monitors will pay particular attention to ensure that the women recruited to participate in the study fulfill eligibility criteria, enrollment is progressing adequately, informed consent is appropriately documented, providers adhere to the randomization scheme, data are appropriately reported, and protocol violations/deviations are avoided. Any deviations from the protocol or practices that elicit concern on the part of the monitor will be discussed with the sites’ Investigator(s) and corrective measures will be taken.

***Analysis and Dissemination of Results***

Bivariate analyses will be conducted, stratified by study arm. Unadjusted and adjusted logistic regression will be conducted respectively for categorical and continuous dependent variables.

To compare the two study arms (oxytocin IM vs. oxytocin infusion), the main analyses will include:

- Mean postpartum blood loss (primary outcome)
- % of women with blood loss ≥500 ml (primary outcome)
- Median postpartum blood loss and interquartile range
- % of women with blood loss ≥1000 ml,
- Mean change in Hb measured pre- to post-delivery
- % of women with postpartum Hb drops of 2 g/dl or greater
- % of women with prolonged third stage of labor
- % of women who received additional oxytocics or other interventions to manage bleeding
- % of women who experienced side effects

We will register use of any other AMTSL components, such as controlled cord traction, uterine massage, etc. that are used.

In order to assess the relationship between shock index and severity of bleeding, we will correlate shock index values, heart rate, and blood pressure measures to blood loss levels that will be recorded at 15, 30, 45, and 60 minutes following delivery. Absolute values and measured changes in these values during the first hour following delivery will be analyzed. We will also explore associations between these clinical signs/symptoms with other PPH outcomes, including provision of additional interventions to control bleeding, blood transfusion, and other severe outcomes.

Data will be owned by Gynuity Health Projects. The principal investigators and study coordinators will work together to analyze the results of the study and prepare at least one manuscript for submission to one or more relevant peer-reviewed journals. In addition, members of the study team will present the results of the study at conferences and meetings where appropriate. All principal investigators will be named along with key Gynuity staff as authors of any publications or presentations describing results from the study.

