While a comparison of IV and IM administration of oxytocin during the third stage of labor has not been rigorously explored, authors of several papers question a potential effect of the route of administration, particularly in relation to speed of delivery and its effect on preventing postpartum blood loss. An unpublished secondary analysis from a large clinical trial in which women received oxytocin prophylaxis in the third stage of labor suggests that route of administration matters, particularly when oxytocin is the only AMTSL component provide. Mean postpartum blood loss was 336 ml among women who received only oxytocin IM prophylaxis in the third stage of labor (n=2845) and was 60 ml lower (277 ml) among women who received only oxytocin IV prophylaxis (n=785). The women who received oxytocin prophylaxis via IV had a reduced risk of postpartum blood loss 700ml compared to women who received oxytocin IM (OR 0.24, 95% CI 0.12-0.51). The probability of such blood loss was 0.5% instead of 2.1%. Of the 785 women who received oxytocin by IV, the vast majority of women receiving oxytocin IV were given bolus injections. Forthcoming results from a WHO-sponsored study on the components of AMTSL will include a comparison of the effect of IV and IM oxytocin on PPH. Another study found that IV bolus of oxytocin resulted in a statistically significant lower estimated mean blood loss as compared to IV infusion of oxytocin (358 ml vs 424 ml, p=0.029). In this study, blood was not measured in a calibrated container and blood loss was estimated by clinical providers’ visual assessments, however it does raise the question of whether IV bolus and IV infusion are as similar as they are assumed to be.

Oxytocin is widely considered to be a safe drug when used prophylactically to prevent PPH. Side effects are uncommon in women who deliver vaginally, however nausea and vomiting have been reported . A study comparing maternal hemodynamics after oxytocin bolus or infusion in the third stage of labor following vaginal delivery showed that bolus administration of oxytocin 10 IU is not associated with adverse hemodynamic responses and can safely be administered to women with intravenous access in the third stage of labor for postpartum hemorrhage prophylaxis.

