**Explanation of Sample Size**

The primary outcomes of the study are (1) mean blood loss and (2) the proportion of women with PPH (defined as ≥500 ml).

This study is designed to detect a 50 ml difference in mean blood loss after provision of oxytocin prophylaxis via IV infusion and IM injection. In the published literature, a 50 ml difference has been shown to translate to approximately a 50% reduction in PPH rates (≥500 ml) . Based on the assumption that oxytocin prophylaxis IV will yield a mean blood loss of 275 (SD175)we estimate that a total of 257 women would be required in this superiority trial to detect a 50 ml difference in mean blood loss between the two groups with 80% power at a significance level of 0.05.

A prior study of PPH conducted at Hospital Vida had documented a rate of blood loss ≥500 ml of 18%, among women who received prophylactic oxytocin (10 IU) in the third stage of labor and with blood loss objectively assessed using a calibrated receptacle. Based on the assumption that oxytocin prophylaxis IV will yield a clinically meaningful reduction of at least 50% in the proportion of women with blood loss ≥500 ml , we calculate that a total of 442 women (vaginal deliveries) (221 per group) are required in this superiority trial to compare a 18% PPH rate following IM injection and a 9% PPH rate following IV infusion with 80% power at a significance level of 0.05. The sample size will be increased by 10% to account for any loss to follow up or missing blood loss readings for assessment of both primary outcomes. Thus, **a total sample size of 486 (243 per arm) is required** for the study in Ecuador. This sample size will be sufficient to detect a 50 ml mean difference in blood loss between study groups.

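### The only model named for categorical outcomes, logistic regression, suits loss ≥1000 ml badly: with about 3 to 6 expected events an arm may well have none, and the odds ratio is then not finite

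*Protocol*

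**What the plan says.** The section Analysis and Dissemination of Results of the protocol promises bivariate analyses by arm and then one modelling sentence: "Unadjusted and adjusted logistic regression will be conducted respectively for categorical and continuous dependent variables". Among the main comparisons of the two arms it lists the percentage "of women with blood loss ≥1000 ml". The Research Objectives make the same threshold a secondary objective. The Background adds that use of other components of active management will be controlled for in the analysis.

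No rate, expected count or power is given for loss ≥1000 ml. The nearest information is:

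- Explanation of Sample Size: oxytocin IV "will yield a mean blood loss of 275 (SD175" ml, with a 50 ml difference to be detected.
- Explanation of Sample Size: "18% PPH rate following IM injection and a 9% PPH rate following IV infusion with 80% power at a significance level of 0.05", for loss ≥500 ml.
- Explanation of Sample Size: "a total sample size of 486 (243 per arm) is required", after a 10% increase from 442 (221 per group).
- Background, on 700 ml of blood loss in an earlier trial, IV against IM: "The probability of such blood loss was 0.5% instead of 2.1" percent.

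**The concern.** Maximum-likelihood logistic regression needs events in both arms. If one arm has none, the estimated odds ratio is 0 or infinite, the standard error grows without limit, and the Wald test and interval carry no information. If neither arm has an event, nothing can be estimated.

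The risk is that a model failure is read as a finding of no difference in severe haemorrhage. With 0 v 6 events among 243 per arm, Fisher's exact test gives p = 0.03, while the Wald output for the same table is uninformative. Without an empty arm the model runs but says little: 1 v 4 events gives an odds ratio of 0.25 with a Wald 95% interval of 0.03 to 2.2.

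**Working it through.** **The plan's own figure.** For 18% v 9%, two-sided 5% (sidedness is not stated, so this is assumed) and 80% power, the usual formula gives 226 per arm with pooled variance and 223 unpooled. The stated 221 is within 3% of either and has 79.3% power. The inflation is 442 × 1.10 = 486.2, so 486, or 243 per arm, is reproduced.

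**Tail at 1000 ml.** The protocol gives no such rate, so a shape must be assumed. For a lognormal, s² = ln(1 + (SD/mean)²), m = ln(mean) − s²/2 and P(≥x) = 1 − Φ((ln x − m)/s).

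IV arm, mean 275, SD 175:
- s² = ln(1 + (175/275)²) = 0.3400, s = 0.5831, m = 5.4468.
- At 500 ml this gives 9.4%, close to the plan's 9%.
- At 1000 ml, z = (6.9078 − 5.4468)/0.5831 = 2.506, so P = 0.00611.

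IM arm, three ways:
- A. Mean 325, SD 175: s = 0.5046, m = 5.6565, z = 2.480, P = 0.00657.
- B. Mean 325, same coefficient of variation (SD = 325 × 175/275 = 206.8): s = 0.5831, m = 5.6138, z = 2.219, P = 0.01324.
- C. Keep s = 0.5831 and shift both arms to match 9% and 18% at 500 ml. The z value rises by ln 2/0.5831 = 1.1887 between 500 and 1000 ml. IV: 1.3408 + 1.1887 = 2.5295, P = 0.00571. IM: 0.9154 + 1.1887 = 2.1041, P = 0.01769.

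**Expected events and the chance of an empty arm.** Events = n(pIV + pIM). With a = (1 − pIV)^n and b = (1 − pIM)^n, the chance that at least one arm is empty is a + b − ab.

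| Scenario | Events, n = 243 | a + b − ab, n = 243 | Events, n = 221 | Chance, n = 221 |
|---|---|---|---|---|
| A | 3.1 | 0.2254 + 0.2014 − 0.0454 = 0.38 | 2.8 | 0.43 |
| B | 4.7 | 0.2254 + 0.0392 − 0.0088 = 0.26 | 4.3 | 0.30 |
| C | 5.7 | 0.2486 + 0.0131 − 0.0033 = 0.26 | 5.2 | 0.30 |

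**Sensitivity to shape.** With means 275/325 and SD 175 at 243 per arm, a gamma shape gives 1.5 events and a chance of 0.73; a normal shape gives 0.02 events and a chance near 1. Of the shapes tried at these means and SD, lognormal is the kindest to the plan.

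**Sensitivity to effect, on curve C at 243 per arm.**
- 18% v 13.5% at 500 ml: pIV = 0.01096, 7.0 events, chance 0.0687 + 0.0131 − 0.0009 = 0.08.
- 18% in both arms: 8.6 events, chance 0.0131 + 0.0131 − 0.0002 = 0.03.

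**Cross-check.** The Background rates at 700 ml, if they applied here, give 243 × (0.005 + 0.021) = 6.3 events and a chance of 0.30, and events at 1000 ml would be fewer.

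**The case against.** Four arguments for the plan deserve weight.

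1. The bivariate analysis by arm already covers this outcome, so the percentages will be reported whatever the model does. This stands. A reader might infer that the secondary objective cannot be answered; the documents do not support that. Only the regression estimate fails.

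2. Exact tests and sparse-data rules commonly sit in a statistical analysis plan. This stands as far as silence goes: the lack of a named test for the bivariate comparison is no fault by itself. It does not cover a model that the protocol does name and that fits this outcome badly.

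3. The size depends on assumptions. The count of 3 to 6 needs a lognormal shape. Scenarios A and B give only 13.4% and 15.1% for IM at 500 ml, against the planned 18%; curve C matches both planned rates and gives 26%. The chance also drops quickly if the effect is smaller than planned. All of this stands and limits the point.

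4. A reader might infer that an adjusted logistic model is fixed for every binary outcome. Read literally, the word respectively gives categorical outcomes the unadjusted model only. The Background's intention to control for other components of active management suggests adjustment but fixes no model or covariates, so no failure rate for an adjusted model can be derived from the protocol. The figures above concern the unadjusted model and hold on either reading.

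Nor can the point be carried over to transfusion and hysterectomy as separate comparisons. The main analyses compare arms on additional oxytocics or other interventions taken together; transfusion is named separately only in the exploratory shock-index work.

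**Conclusion.** The point holds, at low severity. Logistic regression is the only model named for categorical outcomes, and it is a poor choice for loss ≥1000 ml. Under a lognormal shape and the planned effect, about 3 to 6 events are expected in 486, and an empty arm occurs in about 26% to 38% of trials (30% to 43% at 221 per arm). Thinner-tailed shapes make this more likely; a smaller true effect makes it less likely, down to about 8% and 3% on the calibrated curve.

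The event count is an inference under stated assumptions, since the protocol gives no rate at this threshold. The sentence has a further fault: as worded, it assigns logistic regression to continuous outcomes, which include the primary outcome of mean blood loss.

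**What to change.** In Analysis and Dissemination of Results, state that for loss ≥1000 ml, and for any other binary outcome with very few events, the report gives counts per arm, the risk difference with a score or exact 95% confidence interval, and an exact test, in place of the maximum-likelihood logistic model. State what counts as very few before unblinding, so that the method is not chosen from the results by arm. If a regression estimate, or one adjusted for components of active management, is wanted, use Firth-penalised logistic regression with minimal adjustment. Logistic regression can stay for loss ≥500 ml.

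In the same edit, remove the word respectively, name a model suited to continuous outcomes such as linear regression, and say for each outcome type whether estimates are unadjusted, adjusted or both.

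The cost is a few sentences and no new data. The downside is that intervals for the sparse outcomes will be wide and largely unadjusted.
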